## Sample size

Sample size calculations were performed using PS: Power and Sample Size Calculation software. With a power of 0.80, an  $\alpha$  of 0.05, a non-inferiority margin of 0.07 and an expected proportion of 0.96, this resulted in a sample size of 97 (we choose 100) patients per group when using an uncorrected chi-squared statistic.

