## 6 CLINICAL INVESTIGATION DESIGN

### 6.1 General

This clinical investigation is designed as a single center patient preference trial in a tertiary hospital in the Netherlands. We will test for non-inferiority of the outcome of the outpatient recovery after standard bariatric surgery compared to the current treatment, as well as evaluate the feasibility of the outpatient recovery after standard bariatric surgery.

To avoid bias, patient preference for either the current recovery path (group B) or the outpatient recovery (group A) after standard bariatric surgery is noted to be able to include the preference factor in the analysis. The patients that don't have a preference will be randomly assigned. The number of patients included in each group will be equal.

The primary endpoint of the study is the combined outcome measure, based on the following:

- Mortality
- Severe postoperative complications (Clavien-Dindo IIIb or higher)
- Readmission (at least one night in hospital)
- Mild complications (Clavien-Dindo II and IIIa)
- Prolonged length of stay (3 days or more in hospital)

within 30 days after primary surgery.

The secondary endpoints of the study are:

- Patient satisfaction >6 points (on a scale of 1-10)
- Percentage of patients recruited for the outpatient recovery after standard bariatric surgery group
- Percentage of patients with full adherence to protocol and randomization
- Percentage of missing data

|                                                                                                                    |              |                        |                  |                    |
|--------------------------------------------------------------------------------------------------------------------|--------------|------------------------|------------------|--------------------|
| Title: Clinical Investigation Plan                                                                                 |              | Author: [name] |                  | Philips restricted |
| DocID: ICBE-2-36455                                                                                                | Version: 3.0 | Date: 2020-DEC-08      | Status: Approved | Page: 22 of 44     |
| This document is based on Philips Research Template: Clinical Investigation Plan, ID: QR-TEM-57, Date: 2019-Mar-21 |              |                        |                  |                    |

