## Statistical design

This study is primarily designed to test for non-inferiority of outpatient recovery compared to regular treatment for bariatric surgery. The outcome measure that we will use for the analysis is a combined measure, based on the following:

- Mortality
- Severe postoperative complications (Clavien-Dindo IIIb or higher)
- Readmission (at least one night in hospital)
- Mild complications (Clavien-Dindo II and IIIa)
- Prolonged length of stay (3 days or more in hospital)

within 30 days after primary surgery.

We choose to use this combined outcome measure since it is in line with other surgical studies [5] making it comparable to literature.

I current practice at Catharina Hospital, Eindhoven, 95% of all bariatric surgery patients do not have any of these events which is considered the textbook outcome here.

We set the following null and alternative hypotheses for proving non-inferiority:

$H_0: p_{\text{regular}} - p_{\text{outpatient}} \geq \Delta$

$H_1: p_{\text{regular}} - p_{\text{outpatient}} < \Delta$

Where  $p_{\text{regular}}$  is the textbook outcome proportion in the regular treatment group, and  $p_{\text{outpatient}}$  is the textbook outcome proportion in the outpatient recovery group. We will use a non-inferiority margin ( $\Delta$ ) of 7%, which is deemed clinically significant by the Principal Investigator. This is also justified by a previous study where the average textbook outcome across bariatric surgery patients in the Netherlands was 88,7% [5] which helps to derive a non-inferiority margin of around 7% to the one seen at Catharina Hospital. We will use an uncorrected chi-squared statistic. Based on the sample size calculation done below an p value of 0.05 will be considered statistically significant. For the interim analysis an alpha correction for multiple testings is applied and a p value of 0.025 will be considered statistically significant.

The secondary endpoints will be analysed statistically in analogy to the primary endpoint by uncorrected chi-squared statistic where deemed appropriate.

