## Missing Data

No replacement of missing data will be performed and the affected measurements will be regarded as lost for final statistical analysis.

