### Expected drop-out rates

The expected drop-out rate is 10% (20 patients in this sample). Patients dropping out during the first 2 days of the study will be replaced until the final 200 patients are included and have participated more than the 2 days defined for replacement.

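### The sample size assumes a 96% textbook-outcome rate, but the protocol gives 95% for this hospital; at 95%, 100 per group gives about 73% power, not 80%

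*Protocol*

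**What the plan says.** All of this is in section 7 of the protocol unless noted.

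- **Statistical design** defines the textbook outcome as the absence of every component of the composite within 30 days. For current practice at the study hospital it says that "95% of all bariatric surgery patients do not have any of these events". The margin is 7 percentage points, and "an p value of 0.05 will be considered statistically significant". It does not say whether the test is one-sided or two-sided.
- **Sample size** begins "With a power of 0.80", takes "a non-inferiority margin of 0.07 and an expected proportion of 0.96", and reports that "this resulted in a sample size of 97 (we choose 100) patients per group". Neither a source for 0.96 nor a reason for departing from 95% is given.
- **Section 6.1** fixes equal groups: "The number of patients included in each group will be equal". It also says that the principal investigator takes every component of the primary endpoint from the medical record.
- **Expected drop-out rates** expects 10%, or 20 patients. Those who leave in the first 2 days are replaced until 200 have passed that point. Section 6.3 has a similar replacement rule.
- **Missing Data** rules out imputation and says that "the affected measurements will be regarded as lost for final statistical analysis".

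**The concern.** Two adjoining paragraphs give different success rates for what should be the same planning quantity. Near the ceiling, one percentage point matters: the variance term p(1−p) rises from 0.0384 at 96% to 0.0475 at 95%, which is 24% more. A sample size that just reaches 80% power at 96% therefore cannot reach it at 95%.

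The Pass/fail criteria make the non-inferiority conclusion the test of the study's success, and the power statement is the protocol's quantitative case for 200 patients. If power is really about 73%, the chance of failing to show non-inferiority when the two recovery paths are equal is about 27%, not 20%. A negative result would then say less than readers would assume.

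A secondary question is whether drop-out lowers power further. The step from 97 to 100 leaves a reserve of only 3 patients per group, drop-outs after day 2 are not replaced, and the endpoint runs to day 30.

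**Working it through.** **Inputs.** Margin 0.07, power 0.80, alpha 0.05 and rate 0.96 (Sample size); rate 0.95 (Statistical design); 100 per group, equal allocation (Sample size, section 6.1). One-sided alpha is an assumption, tested in step 1.

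**Step 1: reproduce the protocol's 97.** With the same rate p in both groups and no true difference,

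n per group = (z₀.₉₅ + z₀.₈₀)² × 2p(1−p) / margin²

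= (1.6449 + 0.8416)² × 2 × 0.96 × 0.04 / 0.07² = 6.183 × 0.0768 / 0.0049 = 96.9, rounded up to **97**.

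This matches exactly. The other variants tried do not:

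| Variant | n per group |
|---|---|
| 0.96 in both groups, one-sided 0.025 | 124 |
| Pooled test of 0.96 against 0.89, one-sided / two-sided 0.05 | 175 / 222 |
| The same with continuity correction | 202 / 249 |
| 0.95 regular and 0.96 outpatient, one-sided 0.05 | 83 |

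The last row uses 6.183 × (0.0475 + 0.0384) / 0.08². It shows that reading 0.96 as a hoped-for outpatient rate against 95% in regular care does not explain the 97.

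**Step 2: put in the protocol's own 95%.**

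n = 6.183 × 2 × 0.95 × 0.05 / 0.0049 = 6.183 × 0.095 / 0.0049 = 119.9, rounded up to **120 per group**.

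**Step 3: power with 100 per group.**

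Power = Φ(0.07 / √(2p(1−p)/n) − 1.6449)

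- At 96%: √(0.0768/100) = 0.02771; 0.07/0.02771 = 2.526; Φ(0.881) = **81.1%**.
- At 95%: √(0.095/100) = 0.03082; 0.07/0.03082 = 2.271; Φ(0.626) = **73.4%**.

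Only 5 failures per group are expected at 95%, so the normal approximation was checked against exact binomial power of the same Wald test. This gives 73.0% at 95% and 80.1% at 96%, both with 100 per group.

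**Step 4: drop-out, as a bound only.** If the full 10% were lost from the analysis, 90 per group would remain:

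| Rate | Analysed per group | Formula | Exact |
|---|---|---|---|
| 96% | 100 | 81.1% | 80.1% |
| 96% | 90 | 77.4% | 78.0% |
| 95% | 100 | 73.4% | 73.0% |
| 95% | 90 | 69.5% | 71.4% |

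**Step 5: sensitivity to sidedness.** If the test were one-sided at 0.025, 100 per group would give 71.4% at 96% and 62.2% at 95%. One-sided 0.05 is therefore the reading more favourable to the plan, as well as the one that returns 97.

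**The case against.** **The rates may not truly conflict.** The margin is explained as roughly the gap between a national average of 88.7% and this hospital's rate. Adding 7 points gives 95.7%, which rounds to 0.96. At 95.7% the formula gives 104 per group and 78.7% power with 100. The 95% also describes bariatric patients in general, whereas the trial takes primary sleeve or bypass patients with further exclusions, who might do slightly better. Neither argument removes the problem. The margin is described only as around 7%, and 95% fits that wording too (95 − 88.7 = 6.3). A rate worked back from a rounded margin does not displace one stated outright. The protocol does not offer case selection as its reason.

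**Sidedness is inferred.** This stands, and the result should carry that label.

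**Drop-out.** A reader might set the 3-patient reserve against the 10% drop-out and conclude that power is 69%. The documents do not support that. It needs all 10% to leave after day 2, none to be replaced, and none to have a 30-day outcome. Early leavers are replaced, and the split of the 10% is not stated. Section 6.1 takes the outcome from the medical record, and the Schedule of Activities places CRF completion at day 31. The Study population paragraph analyses randomised patients as assigned, whatever treatment they received. A patient who stops wearing the device need not lose the endpoint. What remains is a gap in wording: nowhere does the protocol say that such patients stay evaluable, while Missing Data treats absent values as lost.

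**Consequence.** A reader might also infer a greater risk of a false non-inferiority claim. That does not follow, because the planning rate affects type II error only.

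**Conclusion.** The point holds for the rate. The 80% power statement depends on a 96% rate that disagrees, without explanation, with the 95% given in the adjoining paragraph. On the protocol's own 95%, 100 per group gives about 73% power (73.4% by formula, 73.0% exact), and 80% needs 120 per group. This assumes a one-sided alpha of 0.05, equal true rates in the two groups and all 100 per group analysed.

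Drop-out is secondary. Its effect ranges from none to a worst case of about 69–71% at the 95% rate, and the record-based endpoint makes little or no loss the more likely reading.

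This should be corrected, but it does not threaten the validity of a positive result. Confidence is high for the mismatch and its effect on power, and low for any drop-out effect.

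**What to change.** 1. Use one textbook-outcome rate in Statistical design and Sample size. If 95% is right, restate Sample size as: about 73% power with 100 per group, one-sided alpha 0.05. If 96% is right, correct Statistical design and give its source.
2. State the sidedness of the test in either case.
3. In Missing Data and Expected drop-out rates, say that patients who stop after day 2 keep their 30-day outcome, read from the medical record, unless they withdraw consent for this.

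The cost is a few sentences and, if 95% is right, a less favourable power figure. No new data collection is needed, as the record review and day-31 CRF completion are already planned. Restating the power does not restore it: if the sponsor wants 80% at 95%, the price is 120 analysed per group, or 240 instead of 200.

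### The 80% power rests on a 96% textbook-outcome rate, but the protocol gives the site's own rate as 95%, at which 100 per group has about 73% power

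*Protocol*

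**What the plan says.** Section 7 of the protocol gives two values for the textbook-outcome proportion, the complement of the composite primary endpoint.

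- Under Statistical design, the site's current practice is described: "95% of all bariatric surgery patients do not have any of these events which is considered the textbook outcome here".
- Under Sample size, the calculation uses "an expected proportion of 0.96, this resulted in a sample size of 97 (we choose 100) patients per group". It starts "With a power of 0.80" and applies "when using an uncorrected chi-squared statistic".

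The margin is 7 percentage points. It is attributed first to the Principal Investigator's clinical judgement. It is then also supported by a published national average of 88.7%, "which helps to derive a non-inferiority margin of around 7" percent. On the significance level, the text says only that "an p value of 0.05 will be considered statistically significant". It does not say whether this is one-sided or two-sided.

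On losses, the protocol says: "The expected drop-out rate is 10% (20 patients in this sample"). Drop-outs in the first two days are replaced until 200 patients have passed that point (Expected drop-out rates, and the withdrawal criteria in Section 6.3). Missing data are not imputed (Missing Data). The components of the primary endpoint are read from the medical record (Section 6.1).

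**The concern.** Both proportions are given for the same composite at the same single hospital, and the protocol does not explain the difference. At proportions this close to 1, a single point changes the variance noticeably: p(1-p) is 0.0384 at 96% and 0.0475 at 95%, an increase of 24%. The required sample size rises in the same ratio.

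The study passes or fails on whether non-inferiority can be concluded. If the site's rate of 95% holds in both groups, a truly equivalent pathway would fail to show non-inferiority in about 27% of such trials, not 20%. An inconclusive result could then be read as coming from a study with 80% power, which on the protocol's own rate it is not. The problem is confined to power: the mismatch does not raise the risk of a false claim of non-inferiority.

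**Working it through.** **Inputs.** Margin 0.07, alpha 0.05, power 0.80, equal groups, 100 per group chosen, p = 0.96 (Sample size) or 0.95 (Statistical design). The true difference is taken as zero.

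**Step 1: reproduce the plan's figure.** The non-inferiority formula with unpooled variance is

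n per group = (z_alpha + z_power)² × 2p(1-p) / margin²

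With one-sided alpha 0.05 and p = 0.96: (1.645 + 0.842)² × 2(0.96)(0.04) / 0.07² = 96.9, so 97. This matches the protocol.

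The other readings that were tried do not give 97:

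| Reading | n per group |
|---|---|
| 96% in both groups, one-sided 0.05 | 97 |
| 96% in both groups, one-sided 0.025 | 124 |
| 95% regular, 96% outpatient, one-sided 0.05 | 83 |
| 96% regular, 95% outpatient, one-sided 0.05 | 148 |
| Ordinary comparison of 96% with 89%, one-sided / two-sided 0.05 | 175 / 222 |

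So 96% was applied to both groups, including the regular-care group, and alpha was one-sided.

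**Step 2: the same formula at 95%.** (1.645 + 0.842)² × 2(0.95)(0.05) / 0.07² = 119.9, so 120 per group.

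**Step 3: power at the chosen size.** Power = Φ(margin / √(2p(1-p)/n) - 1.645), one-sided alpha 0.05.

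| True rate, both groups | n = 100 | n = 90 |
|---|---|---|
| 96% | 81.1% | 77.4% |
| 95% | 73.4% | 69.5% |

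At 95% and n = 100: 0.07 / √(0.095/100) = 2.271; 2.271 - 1.645 = 0.626; Φ(0.626) = 73.4%.

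**Step 4: exact check.** Summing binomial probabilities at 95% with 100 per group gives 73.0% for the unpooled Wald test. A score test with variance restricted to the null gives 68.2%. At 90 per group the exact Wald figure is 71.4%, so the normal approximation of 69.5% is slightly pessimistic there.

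**Step 5: the margin sentence.** 95% - 88.7% = 6.3 points, and 96% - 88.7% = 7.3 points. Seven points below 95% is 88.0%, which is 0.7 points under the national average. Seven points below 96% is 89.0%, which is above it.

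**The case against.** The arithmetic in the Sample size paragraph is right for its own inputs. What is at fault is an unexplained assumption.

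It is also not settled that 95% is the better figure. The national 88.7% plus 7 points is 95.7%, which rounds to 96%, so the margin sentence fits 96% at least as well. The 95% describes all bariatric patients at the hospital, whereas the trial enrols selected primary sleeve or bypass patients, who might do a little better. This part of the objection stands: the first request must be to reconcile or justify the rates. It does not rescue the text as written, because the protocol gives no such reason and states 95% as the site's current rate.

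Three stronger readings are tempting, and the documents do not support them.

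- **That power is 69% once the stated 10% drop-out is applied.** This treats all 20 drop-outs as missing primary outcomes. Early drop-outs are replaced, analysis is by intention to treat, and the 30-day outcome comes from the medical record and not from the device or the questionnaire. Withdrawal of consent may end access to some records, but the protocol gives no number for that. So 69% is the lower end of a range, not the expected power.
- **That alpha is two-sided, so power at 95% is only 62%.** The hypotheses are directional and 97 arises only with one-sided 0.05. The 62% describes a test on which the trial was not sized. What is missing is the label.
- **That the margin is miscalculated.** It rests first on clinical judgement. The national figure is offered as further support, and the result is called approximate. The gap of 0.7 points concerns wording.

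**Conclusion.** The point holds for the mismatch of rates. The claim of 80% power depends on 96% in both groups; at the protocol's own 95%, 100 per group gives about 73%, and 80% would need 120 per group. With 95% and one-sided alpha 0.05, power ranges from about 73% if every 30-day outcome is obtained to about 69% if 10% are lost after the replacement window and not recovered.

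These figures assume equal true rates, a 7-point margin, one-sided alpha 0.05 and the unpooled test that reproduces 97. A score test would give less (68.2% exact, 100 per group). If a documented basis for 96% exists, power at 100 per group is 81% and the fault reduces to a missing explanation. The unstated sidedness and the margin wording are secondary.

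**What to change.** In Section 7:

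1. Reconcile 95% with 96%. Either give the basis for expecting 96% in the trial population, or use 95% in the Sample size paragraph.
2. State that alpha 0.05 is one-sided.
3. If 95% is used, replace the 80% claim with wording such as: with 100 evaluable patients per group, 95% in both groups, a 7-point margin and one-sided alpha 0.05, power is about 73%; in the worst case, with 10% of 30-day outcomes lost after the replacement window and not recoverable from the medical record, it is about 69%.
4. In the margin sentence, show that 95% - 88.7% is 6.3 points and that a 7-point margin from 95% allows 88.0%, slightly below the national average.

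The cost is one corrected paragraph, one corrected sentence and a less favourable stated power. The number of patients, the margin and the test stay as they are.

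### At 100 patients per group the stated alpha of 0.05 and power of 0.80 are not delivered together, and the named test does not say which of the two gives way

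*Protocol*

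**What the plan says.** Section 7 of the protocol fixes the test, the level, the power and the size.

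- Sample size: "With a power of 0.80", an alpha of 0.05, "a non-inferiority margin of 0.07 and an expected proportion of 0.96"; then "this resulted in a sample size of 97 (we choose 100) patients per group when using an uncorrected chi-squared statistic".
- Statistical design: the null hypothesis is that the textbook-outcome proportion under regular care exceeds that under outpatient recovery by at least 7 points. On the test: "We will use an uncorrected chi-squared statistic". On the level: "an p value of 0.05 will be considered statistically significant".
- Statistical design also gives the site's current rate: "95% of all bariatric surgery patients do not have any of these events".
- Section 6.1: "The number of patients included in each group will be equal".

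Section 7 does not say whether the 0.05 is one-sided or two-sided, or how a chi-squared statistic is to be set against a 7-point margin. It mentions no check of the large-sample approximation.

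**The concern.** At 96% success, a group of 100 has only 4 expected failures. The sample-size formula and an uncorrected statistic both treat the difference in proportions as normal, with a variance that is in effect known. With so few failures that is a rough approximation, so the true error and power can differ from the nominal ones.

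The wording of the test adds to this. The ordinary uncorrected chi-squared tests equality. Against a margin it has two natural counterparts: a z statistic with the observed variance (pooled or unpooled), or a score statistic with the variance estimated under the null hypothesis. With small counts these are different tests.

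At stake are the two figures on which the design rests. Either the chance of wrongly declaring same-day discharge non-inferior is above the stated 5%, on an endpoint that includes death and severe complications, or the trial has less than the stated 80% power. If the form of the test is left open, a result near the boundary could also be read either way once the data are known.

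**Working it through.** **Inputs** (protocol, section 7): proportion 0.96 in both groups, margin 0.07, alpha 0.05, power 0.80, equal groups of 100. The interim look and later drop-out are left out throughout.

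**1. Reproduce the 97.** One-sided alpha 0.05, true difference zero:

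n = 2 × 0.96 × 0.04 × (1.645 + 0.842)² / 0.07² = 96.9, so 97.

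One-sided 0.025 would give 124, so the plan's 0.05 is taken as one-sided.

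**2. Expected failures.** Under the power scenario: 0.04 × 97 = 3.9, or 4.0 with 100 per group. Under the null at 96% v 89%: 4 and 11.

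**3. Exact operating characteristics.** All pairs of binomial outcomes were enumerated. Non-inferiority is declared if

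(0.07 − (p_regular − p_outpatient)) / SE > 1.645.

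For the simple z, SE uses the observed proportions; at these values, pooled and unpooled variance give the same results. For the Farrington-Manning score test, SE uses the maximum-likelihood proportions restricted to a difference of exactly 0.07.

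| 100 per group | Simple uncorrected z | Score test |
|---|---|---|
| False non-inferiority, 96% v 89% | 5.97% | 4.83% |
| False non-inferiority, 95% v 88% | 5.86% | 4.93% |
| Power, 96% in both groups | 80.1% | 74.6% |
| Power, 95% in both groups | 73.0% | 68.2% |

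Over regular-care rates of 90% to 100%, the score test's error peaks at 5.07%. At the calculated 97 per group, the simple z has 6.6% error and 81.0% power, and the score test 4.4% and 70.9%.

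**4. Is this only a matter of which test is chosen?** A linear programme found the highest power that any test can reach at 96% in both groups while keeping its error at or below 5% along the whole null boundary. At 100 per group it is 75.5%.

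**5. Can the two tests disagree on a plausible result?** Take 3 regular and 5 outpatient failures out of 100 each. The observed difference is 0.97 − 0.95 = 0.02, so the numerator is 0.07 − 0.02 = 0.05.

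- Simple z: SE = √(0.97 × 0.03/100 + 0.95 × 0.05/100) = 0.0277, so z = 1.81, above 1.645: non-inferior.
- Score test: the restricted proportions are about 0.980 and 0.910, so SE = √(0.980 × 0.020/100 + 0.910 × 0.090/100) ≈ 0.032 and z = 1.57, below 1.645: not shown.

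With both groups truly at 96%, the two tests disagree in 5.5% of trials.

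**The case against.** **Nothing is miscalculated.** A reader might infer that the 97 is an arithmetic error. It is not: it follows exactly from the plan's inputs under the large-sample formula. The fault lies in relying on that formula and in not saying which test is meant.

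**The excess is modest.** This stands. At the design values it is about 1 percentage point of error or about 5 points of power, which is no collapse of the approximation. The simple z's error does reach 8.2%, but only with a regular-care rate near 99.5%. The protocol's own rates are 95%, 96% and a national 88.7%, so 8.2% is not a realistic figure for this trial.

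**Small counts are not the whole cause.** This also stands. Four failures per group is the power scenario; the error is judged at 4 and 11. At a 90% regular-care rate, with 10 and 17 expected failures, the simple z still errs at about 5.6%.

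**The conflict is not strict at a single point.** Running the simple z at a nominal level of about 0.038 gives 5.1% error at 96% v 89% with 79.5% power. But the protocol names no such level, and the error elsewhere on the boundary still reaches 8.2%. The 75.5% ceiling applies once error is to be held along the whole boundary.

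**The score version may already be intended, with details left to the SAP.** This is possible, since the score test is the natural chi-squared counterpart with a margin. The level then holds, but the 80% power, which the protocol states itself, does not.

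**More patients must be needed.** A reader might infer this, but the documents do not force it. Exact power of 80% with the score test is first reached at about 118 per group (even sizes from 96 to 130 searched). A sponsor may equally keep 100 and report the power honestly.

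**Conclusion.** The point holds at moderate weight. At 100 per group, with the plan's own 96% and 7-point margin, the trial has either about 80% power with about 6.0% false non-inferiority, or a 5% level with about 75% power. The protocol claims 80% and 5% together, and its wording of the test does not decide between them.

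This rests on a one-sided 0.05 (inferred), equal true rates for the power, and 100 analysed patients in each group. The 75% belongs to 96% only. At the 95% that the Statistical design section gives for the site, the score test has about 68% power. That gap between 95% and 96% is a separate inconsistency of similar size, and the restated power should not conceal it.

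**What to change.** - **Statistical design:** replace the reference to an uncorrected chi-squared statistic, for the primary endpoint, with the one-sided 0.05 Farrington-Manning (Miettinen-Nurminen) score test against the 7-point margin. Equivalently, require the one-sided 95% upper score limit for regular minus outpatient to lie below 0.07.
- **Sample size:** keep 100 per group, and state the exact power of that test as about 75% if both groups are at 96% and about 68% if both are at 95%.

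The cost is a change of protocol or SAP wording and a less favourable stated power. No patients are added. In return the 5% level holds to within about 0.1 point for regular-care rates of 90% and above, and the decision rule is fixed before the data are seen.
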